### Setting

All assessment and interventions will be conducted in a residential long-term care hostel for psychiatric patients in Hong Kong.

### Instruments

The PANSS is a psychiatric rating system that will be used to assess the positive and negative symptoms of schizophrenia exhibited in the week prior to assessment. It is based on information from the reports of family members or primary care staff, as well as a 40-minute semi-structured psychiatric interview with the patient. The patient will then be rated on a scale of 1 to 7 on 30 different symptoms pertaining to 3 different subscales—positive, negative, and general psychopathology—with internal consistency rats ranging from 0.73 to 0.83.

Assessments will be conducted by trained researchers using the following devices:*Psychiatric Symptoms - The Positive and Negative Syndrome Scale (PANSS 30)* [34]*Motor Coordination and Sequencing – Neurological Evaluation Scale (NES)* [35]2.1Motor Coordination Subscale: motor coordination will be measured using four tasks, including (i) tandem walk, (ii) rapid alternation movements, (iii) finger/thumb opposition, and the finger-to-nose test [36]. The ability of the patient to perform each of the above tasks will be rated on a 3-point scale based on the number of mistakes.2.2Sequencing of Complex Motor Acts Subscale: this will consist of four tasks associated with the sequencing of motor acts, including (i) the fist-ring test (right and left hands), (ii) the fist-edge-palm test (right and left hands), (iii) the Ozeretski test, and (iv) the rhythm tapping test [36]. Performance will be rated on a 3-point scale based on the number of mistakes.

3.*Digit Span – Wechsler Adult Intelligence Scale, Third Edition – Chinese version (WAIS-III)* [37] *–* The digit span sub-scale is composed of two parts: forward movement of digits, and backward movement of digits. Participants will be invited to repeat movements of 3*–*9 digits forward and 2*–*9 digits backward. Clinically, the sub-scale evaluates participants’ short-term memory, attention, and concentration.4.*Barthel’s Activities of Daily Living (ADL) index – Chinese version (Barthel’s ADL)* [38] Barthel’s ADL index evaluates basic self-care. The index comprises 10 tasks, including feeding, transferring, grooming, toilet use, bathing, walking, climbing stairs, dressing, and bowel and bladder continence. The items are weighted according to a scheme developed by the authors.5.*Lawton’s Instrumental Activities of Daily Living (IADL) scale – Chinese version* [39] – This self-report scale covers 8 domains of complex daily life, such as ability to use the telephone, shopping, food preparation, housekeeping, laundry, traveling on public transport, self-medication, and the ability to handle finances.6.*Stress*6.1Perceived stress scale (PSS) [40] – The PSS measures how often participants experience general stressfulness within a given month on a 10-item, 5-point Likert scale. Higher scores indicate greater stress. The Chinese version of the PSS was translated and utilized by the research team with good internal consistency.6.2Salivary cortisol – Collection will be conducted by participants themselves under the guidance of mental health professionals. Saliva samples will be collected at four prescribed times (upon awakening, 30 minutes post-awakening, at 11:30 am and at 7:30 pm) using the collection device “Salivette” (Starstedt, Ag & Co., Nümbrecht, Germany), which includes a cotton swab to place under the tongue. Smoking, eating and drinking will be prohibited for half hour prior to saliva collection. The samples collected will be stored at −20°C until analysis.6.3Daily condition measures with salivary cortisol – Measures of participants’ health-related behaviors and activities on the day of saliva collection will be collected in conjunction with salivary cortisol. These measures include (i) self-reported sleep quantity that day (hours of sleep at night and nap hours), (ii) subjective sleep quality rated on a scale of 1 to 10, (iii) smoking habit and the number of cigarettes consumed that day, (iv) alcohol/coffee drinking habits and the approximate amount consumed that day, and (v) subjective evaluation of dietary habits and the quality of diet on the day of collection rated on a scale of 1 to 10. All the above measures will affect the diurnal cortisol rhythm and hence must be taken into account during data interpretation.

7.*Socio-demographic and clinical informat*ion – Patients’ socio-demographic and clinical information will be obtained from personal and medical records. Socio-demographic data include age, gender, education level and marital status. The frequency and duration of exercise or relaxation practices will also be recorded. Clinical information includes the time since psychiatric diagnosis and condition severity, including acute and chronic extrapyramidal symptoms, particularly drug-related movement disorders such as parkinsonism, akathisia and dyskinesia [41]. Medication and other adjunctive treatments, including institutional care, will also be recorded. These factors can represent important confounding variables when modeling outcomes.

### Data analysis

#### Effectiveness of the Tai-Chi intervention

Repeated measures analysis of variance using SPSS software will be used to explore the effectiveness of the Tai-chi intervention over the three assessment time points, relative to the exercise and waitlist control groups. Ordinary least squares (OLS) regression will be used to assess the relationship between the dependent variables (outcomes) and independent variables (covariates). A model of the role of Tai-chi with respect to other influencing variables, such as clinical prognosis or frequency of practice, will deepen understanding of the true effects of Tai-chi in this clinical population. All levels of significance will be set at p < 0.05. Intention-to-treat analysis will be used to prevent participant selection bias due to study discontinuation.

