**Flow diagram of intervention/waitlist control and data collection points.**

### Participant recruitment

Patients diagnosed with chronic schizophrenia, residing in a Hong Kong mental health rehabilitation complex providing both long-term care and halfway house services will be recruited to the study. Patients will be invited to participate by their respective social workers, based on specific inclusion and exclusion criteria.

Inclusion criteria will be as follows: a) fulfillment of DSM-IV TR criteria for schizophrenia, or diagnosis by a psychiatrist, b) age between 18 and 65 years, c) ability to understand and speak Cantonese, and d) no formal training in or regular practice of Tai-chi.

Exclusion criteria will be as follows: a) diagnosis of acute schizophrenia requiring hospitalization, b) presence of unstable or severe schizophrenic symptoms (e.g. persistent withdrawal) that would limit ability to interact or participate in the class, c) history of brain trauma or organic mental disorders (e.g. mental retardation or dementia), d) presence of physical disabilities, e) presence of other severe illnesses which may impair cognitive or visuo-motor function, cause physical pain or limit life expectancy to 10 years or less.

In determining the sample size, we have taken into consideration multiple independent variables, using multiple regression modeling with a medium effect size (f^2^) of 0.15, at 0.8 power and a significance level of 0.05. Experimental, clinical and demographic variables anticipated to affect the intervention outcome were included in the model. An attrition rate of approximately 25% is expected, based on prior community trials of Tai-chi interventions in elderly patients, and exercise programs for patients with severe mental illnesses [33]. Thus, a total of 153 participants will be targeted for the study.

Upon application of inclusion and exclusion criteria, a trained research assistant will obtain informed consent from participants at the rehabilitation complex. Eligible and consenting participants will then be randomized into one of the three treatment conditions, and baseline data collection will be arranged at least one week prior to the commencement of group programs.

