#### Relationship between cortisol levels and physical and psychological deficits

Using baseline data from all participants, correlation analyses will be used to explore the interrelationship between diurnal cortisol patterns and subjective stress, psychiatric symptoms, motor deficits, memory test and general functioning.

To trace individual changes in salivary cortisol levels over time, and to evaluate the complex relationships between different variables, the two-level individual growth curve model [42] and MPlus software will be used for analysis. This method is a variant of multiple regression modeling appropriate for the nested structure of our data sets. In the study, salivary cortisol measures at four time points over the day are nested within participants.

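### The repeated-measures ANOVA named for effectiveness does not, in its standard form, deliver the promised intention-to-treat analysis, because it drops anyone missing one of the three visits

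*Protocol article*

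**What the plan says.** Under *Effectiveness of the Tai-Chi intervention*, the protocol article says that "Repeated measures analysis of variance using SPSS software will be used to explore the effectiveness of the Tai-chi intervention". The comparison takes in baseline, week 12 and week 24, and sets Tai-chi against both other arms. This is the only method it gives for comparing the arms on effectiveness. Later in that paragraph it says: "Intention-to-treat analysis will be used to prevent participant selection bias due to study discontinuation".

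Under *Participant recruitment* it says that "An attrition rate of approximately 25% is expected", and then "Thus, a total of 153 participants will be targeted for the study". Allocation is 1:1:1, so 51 per arm.

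Two other models are mentioned. OLS regression, in the same paragraph as the ANOVA, relates outcomes to covariates. A two-level growth curve model is introduced under the cortisol heading, "To trace individual changes in salivary cortisol levels over time", with the day's four saliva samples nested within participants. Neither is assigned to the arm comparison for symptoms, motor function, memory, daily living or perceived stress, and no imputation is named for those outcomes.

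**The concern.** Repeated-measures ANOVA in its usual SPSS form takes one row per participant and needs every visit in that row. A participant with baseline and week 12 but no week 24 is deleted from the whole analysis, including the week-12 comparison to which that person could have contributed. This is a general property of the method and the software; the article does not state it.

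The set analysed is then defined by completion, which is the selection that the intention-to-treat sentence says it will prevent. Two things are at stake. The first is information: week-12 data already collected go unused. The second is possible bias, if the people who complete differ between arms. Differential loss is plausible, because the trial is non-blind and the arms ask different things of participants: two attend classes for 12 weeks, while the third waits until after week 24.

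**Working it through.** **1. Inputs.** From the article: total 153, 1:1:1 allocation, three assessments, attrition about 25%, and a sample size set "using multiple regression modeling with a medium effect size (f^2^) of 0.15, at 0.8 power and a significance level of 0.05". Assumed here, because the article gives no figures: correlation 0.6 between any two visits, a true Tai-chi versus waitlist effect of 0.50 SD at both follow-up visits, and the dropout mechanisms below.

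**2. The plan's own figure.** The number of predictors k is not stated, so 153 cannot be reproduced without assuming it. With a noncentral F test (noncentrality 0.15 × N; degrees of freedom k and N − k − 1):

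- k = 9 needs N = 114, and 114 / 0.75 = 152.
- k = 11 needs N = 123, and 123 × 1.25 = 153.75, or 154.
- No other k from 2 to 15 comes as close under either inflation.

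The total is therefore consistent with planning for roughly 114 to 123 analysable participants, with the rest treated as lost.

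**3. Size of the analysed set.** If all attrition means at least one missed assessment:

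- 153 × 0.75 = 114.75, about 115 analysed and about 38 excluded.
- Per arm, 51 × 0.75 = 38.25, about 38.
- Over an assumed attrition range of 15% to 35%: 153 × 0.85 = 130 down to 153 × 0.65 = 99.

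Of the 38 or so excluded, those who leave after week 12 have usable week-12 data that the ANOVA discards. The article does not say how loss divides before and after week 12.

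**4. Bias at week 12.** Let higher scores be better, and suppose 25% of each arm is lost after week 12. In the waitlist arm only, the chance of loss rises as the week-12 score worsens. If completers in that arm have a mean week-12 score raised by s, the correlation of 0.6 raises their baseline mean by 0.6s. Their week-12 change is then overstated by s − 0.6s = 0.4s, and the contrast becomes 0.50 − 0.4s. Simulated s, by log-odds slope per SD:

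| Slope | s | 0.50 − 0.4s | Bias |
|---|---|---|---|
| 0.5 | 0.12 | 0.45 | −10% |
| 1.0 | 0.21 | 0.42 | −17% |
| 1.5 | 0.28 | 0.39 | −22% |

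Direct simulation with a million participants per arm gives 0.454, 0.417 and 0.390.

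**5. Other mechanisms, same assumptions.**

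- Random loss in both arms: 0.50, no bias.
- Equally selective loss, 25% in each arm: 0.50 at every slope, no bias.
- One shared mechanism with the same intercept, so that the waitlist arm loses more: 0.493 to 0.457, a bias of 1% to 9%.
- Waitlist-only selection, but with half the loss random and before week 12: 0.474 to 0.434, a bias of 5% to 13%.
- Selection in the Tai-chi arm only, on week-12 score: by symmetry 0.50 + 0.4s, about 0.55 to 0.61, so the effect is overstated.
- Selection in the Tai-chi arm only, on week-12 change with slope 1: 0.676 at week 12 (0.676 − 0.50 = +0.18 SD) and 0.59 at week 24 (+0.09 SD).

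**6. Bias at week 24.** In the waitlist-selective scenarios of step 4, completers' baseline and week-24 means both rise by 0.6s. The two cancel, so the week-24 change contrast stays at 0.50. This cancellation depends on equal correlations and on selection by week-12 score; the last line of step 5 shows that it fails under another mechanism.

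**7. Using all observed data.** In the scenarios of steps 4 and 5 where all loss comes after week 12, an analysis that keeps every week-12 value returns 0.50 at week 12. Predicting the missing week-24 values from baseline and week 12 within arm returns 0.50 at week 24.

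**The case against.** A reader might infer that the ANOVA and the intention-to-treat sentence cannot both hold. The article does not support that. It nowhere says that the analysis is restricted to completers, and both sentences hold if missing visits are imputed before the ANOVA. How missing visits are handled is often left to a full protocol or an analysis plan, neither of which is shown. What survives is narrower: the method is named, the principle is named, and the standard form of the one does not by itself achieve the other.

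The figure of 115 is also conditional. The 25% comes from earlier community Tai-chi trials in elderly patients and from exercise programmes. Here participants live in the facility where they are assessed, so someone who stops classes may still be assessed and fewer may be lost. Intermittent missed visits would push the other way.

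A reader might further take 10% to 22% as the expected bias. That range belongs to a single scenario, in which every dropout has week-12 data and only the waitlist arm drops out selectively. Neither size nor direction can be derived from the article, and zero is within the range.

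Finally, the sample size already allows for attrition. That covers planned power, but it does not address selection, and it is no reason to discard data already collected. The article also does not call the ANOVA primary; the point rests on its being the only between-arm effectiveness method named.

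**Conclusion.** The point holds as a mismatch between the stated method and the stated principle, and it should be fixed. Under listwise deletion the loss of information is certain for anyone assessed at week 12 and missing at week 24. About 115 of 153 would be analysed if the expected attrition is all missed assessments and nothing is imputed.

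Bias is possible but not established. With correlation 0.6 and a true effect of 0.50 SD, it runs from about 0% (loss random, or equally selective in both arms) to about 22% of the week-12 change contrast (loss selective in the waitlist arm only). The direction depends on the arm affected. In those waitlist-selective scenarios the week-24 change contrast is not biased.

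**What to change.** State that the effectiveness analysis is a likelihood-based linear mixed model for repeated measures with arm, visit and arm-by-visit terms and an unstructured covariance, using all available data from all randomised participants. Keep the repeated-measures ANOVA on completers as a sensitivity analysis. Multiple imputation before the planned ANOVA is an acceptable alternative, if the imputation is stated.

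The text should also state the limits. The mixed model is valid if missingness depends on observed data, and it recovers no outcome for people who leave before week 12. A sensitivity analysis for data missing not at random would cover departures from that assumption.

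The cost is a change of wording in the analysis section. SPSS, already named, fits the model through its MIXED procedure, and no extra data, visits or participants are needed.

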**Discussion:**

Based on a promising pilot study conducted prior to this RCT, subjects in the Tai-chi intervention group are expected to be protected against deterioration of motor coordination and interpersonal functioning. They are also expected to have better symptoms management and lower stress level than the other treatment groups.

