## Methods/design

A non-blind, 3-arm randomized controlled trial (RCT) with waitlist control design will be used. Eligible participants will be randomized into (i) Tai-chi, (ii) exercise or (iii) waitlist control groups, on a 1:1:1 basis. The research is conducted in compliance with the Helsinki Declaration, and ethical approval has been obtained from Institutional Review Board of the University of Hong Kong/ Hospital Authority Hong Kong West Cluster (Ref: UW 11–481) before participant recruitment and randomization take place. Human Research Ethics Committee for Non-Clinical Faculties of the University of Hong Kong.

The exercise control will serve as a comparison to delineate the unique benefits of Tai-chi that cannot be accounted for by similar levels of moderate aerobic exercise. This comparison will facilitate a deeper understanding of the positive benefits of Tai-chi, such as attainment of mental tranquility and relaxation, which cannot be explained by physical exercise alone. While exercise is known to confer stress-reducing benefits, there are few studies that compare Tai-chi with alternative exercise interventions [33].

The waitlist control group will continue to receive regular medication and care during the intervention phase. Participants in this group will be offered the Tai-chi or exercise classes on a voluntary basis following completion of the study. Three assessment phases will be carried out for all groups at three time points: (i) baseline, (ii) 12th week (post-intervention time-point), and (iii) 24th week (maintenance time-point).

Figure 1 illustrates the treatment received by the intervention group, the waitlist control condition received by the control group, and the data collection points of the study.

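### The planned repeated measures ANOVA names no Tai-chi versus exercise contrast, and its overall F cannot separate a unique Tai-chi benefit from a benefit shared by both active arms

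*Protocol article*

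**What the plan says.** Under Data analysis (Effectiveness of the Tai-Chi intervention), the article states: "Repeated measures analysis of variance using SPSS software will be used to explore the effectiveness of the Tai-chi intervention", and continues "over the three assessment time points, relative to the exercise and waitlist control groups". The Methods/design section sets the time points at baseline, week 12 and week 24, so baseline enters the ANOVA as a level of the time factor. The threshold is given once: "All levels of significance will be set at p < 0.05". No model term, pairwise contrast or baseline covariate is named. A separate ordinary least squares regression is planned with covariates that are not listed.

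The purpose of the third arm is explicit in Methods/design: "The exercise control will serve as a comparison to delineate the unique benefits of Tai-chi". The main Discussion repeats this aim, seeking benefits beyond those of moderate aerobic exercise. The Discussion part of the Abstract predicts superiority over both comparators: "They are also expected to have better symptoms management and lower stress level than the other treatment groups".

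**The concern.** The question that justifies the exercise arm is a two-arm comparison. The method named for effectiveness is a three-arm, three-visit ANOVA. Its natural overall test, the group-by-time F, responds to any difference in change between any of the arms, including exercise against waitlist. If both active arms beat waitlist by the same amount, the F can be clearly significant while Tai-chi adds nothing to exercise. Unless the contrast is fixed before results are seen, a significant F leaves room to report a benefit as specific to Tai-chi when it is not.

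A second, smaller matter is how baseline is used. As one of three outcome visits it pulls the group main effect towards zero, because randomised arms have no expected difference there. A baseline covariate would make the direct contrast more precise at no cost in data.

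**Working it through.** **Inputs from the article.** Total 153, three arms, 1:1:1; attrition about 25%; three visits; significance level 0.05. Per arm: 153/3 = 51, and 51 × 0.75 = 38.25, so about 38.

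**The plan's own figure.** The 153 comes from "multiple regression modeling with a medium effect size (f^2^) of 0.15, at 0.8 power and a significance level of 0.05", inflated for attrition. The number of predictors is not stated. Nine predictors would give 114, then 114/0.75 = 152, and 153 for equal arms. The figure is therefore compatible with its inputs but not verifiable. It is a regression calculation, so there is no stated ANOVA power to reproduce.

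**Assumed inputs (not in the article).** Unit SD at each visit; equal correlation ρ between visits; effect d reached at week 12 and held at week 24.

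**1. Group-by-time F.** Noncentrality is λ = n × Σ(interaction effects²)/(1 − ρ), with df 4 and 2(3n − 3) = 222.

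- Only Tai-chi works: arm pattern (1, 0, 0), centred (2/3, −1/3, −1/3), sum of squares 2/3.
- Both active arms work equally: arm pattern (1, 1, 0), centred (1/3, 1/3, −2/3), sum of squares 2/3.
- Time pattern (0, 1, 1), centred (−2/3, 1/3, 1/3), sum of squares 2/3.

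So Σ = d² × (2/3) × (2/3) = 0.444d² in both cases. With n = 38, d = 0.5 and ρ = 0.6, λ = 38 × 0.25 × 0.444/0.4 = 10.56 and power is 0.732. Simulation of the case where both arms work (6,000 trials) gave 0.727. The equality holds for every d and ρ.

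**2. Range of that power, 38 per arm.**

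| d | ρ = 0.3 | 0.5 | 0.6 | 0.7 | 0.8 |
|---|---|---|---|---|---|
| 0.5 | 0.46 | 0.62 | 0.73 | 0.86 | 0.97 |
| 0.3 | 0.18 | 0.24 | 0.30 | 0.39 | 0.57 |

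If neither arm works it is 0.05. At d = 0.5 and ρ = 0.6 it is 0.59 if half the effect is lost by week 24, and 0.87 with all 51 per arm.

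**3. Direct contrast.** When Tai-chi and exercise are equal, a Tai-chi versus exercise test on change from baseline rejected in 0.043 to 0.054 of simulated trials in every setting. Read only after a significant overall F, it rejected in 0.046 (d = 0.5, ρ = 0.6).

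**4. Group main effect.** Averaging over three visits shrinks d to 2d/3 = 0.333, and the variance of the mean is (1 + 2ρ)/3 = 0.733. Then λ = 38 × 0.333² × (2/3)/0.733 = 3.84 on 2 and 111 df, and power is 0.39.

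**5. How baseline enters the contrast.** Residual variance at one visit is 2(1 − ρ) = 0.80 for change and 1 − ρ² = 0.64 with baseline as covariate. For a true Tai-chi minus exercise difference of 0.5 SD, with error pooled over the three arms and two-sided 0.05:

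- Change: 0.5/√(0.80 × 2/38) = 2.44, power 0.68.
- Adjusted: 0.5/√(0.64 × 2/38) = 2.72, power 0.77.

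At ρ = 0.5 the pair is 0.58 and 0.70; at ρ = 0.7 it is 0.80 and 0.86.

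**The case against.** The strongest reply is that the article never says effectiveness will be claimed from an overall F. It does not mention an omnibus test, an interaction or a main effect. It names Tai-chi as the index arm and two comparators, which fits pairwise contrasts within the ANOVA, and a condensed article may leave those to an analysis plan that is not shown. This stands. A reader might infer that the trial has committed itself to an omnibus test and will never compare Tai-chi with exercise directly; the text does not support that.

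A reader might also take 73% as the rate of false findings whenever Tai-chi is no better than exercise. That too is unsupported. The figure needs both active arms to beat waitlist by 0.5 SD at correlation 0.6, and the article gives neither value. In that scenario the F is detecting real differences from waitlist, and a statement that Tai-chi beats waitlist would be true. The error lies only in reading the F as Tai-chi over exercise.

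Nor is the F a weak test: when only Tai-chi works, its power is the same 0.73. The complaint is that it is not specific.

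Finally, it would be too strong to say that baseline is ignored. The interaction compares changes from baseline, and the regression covariates are unlisted, so adjustment there is neither stated nor excluded. Between randomised arms, change score against covariate adjustment is a matter of precision, not validity.

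What remains is that the article does specify its effectiveness method, and that method, as worded, is not tied to the comparison it calls central.

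**Conclusion.** The concern holds in a limited form. The effectiveness analysis names no Tai-chi versus exercise contrast, and an overall group-by-time F cannot supply one, because it responds identically to a benefit unique to Tai-chi and to a benefit shared with exercise. That identity depends on no assumed effect size or correlation, given the same effect pattern over time and equal arms.

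The size does depend on assumptions: 0.73 is one illustration in a range from 0.05 to 0.97 over the settings tried. Only the 38 per arm derives from the article. The loss from not conditioning on baseline is modest, about 9 percentage points of contrast power at correlation 0.6 (0.68 against 0.77). The group main effect, at 0.39, would be a poor basis for any conclusion. This is worth changing before results are seen, but it does not show that the trial would reach a false conclusion.

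**What to change.** State in the Data analysis section that the effectiveness conclusion rests on two 1-df contrasts at week 12, Tai-chi minus exercise and Tai-chi minus waitlist, each reported as an estimate with a 95% CI. Take both from a model with weeks 12 and 24 as outcomes and the baseline value of the outcome as covariate; the week 24 contrasts then address maintenance. Add that no claim of a benefit unique to Tai-chi will rest on the overall F alone. If pairwise contrasts are already in a fuller plan, citing them here and stating how baseline enters would be enough.

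The cost is analysis wording only. All three assessments are already collected, so no new data, visits or participants are needed.

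### A regression that adjusts Tai-chi for frequency of practice does not estimate the randomised effect, and can shrink, remove or reverse the Tai-chi coefficient, mainly against waitlist

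*Protocol article*

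**What the plan says.** The Data analysis section on effectiveness describes two analyses.

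- A repeated measures ANOVA compares the three arms over baseline, 12 and 24 weeks. No covariates are named, and intention-to-treat is stated.
- An OLS regression relates outcomes to covariates. It is introduced as "A model of the role of Tai-chi with respect to other influencing variables, such as clinical prognosis or frequency of practice", and the same sentence says it will improve understanding of what Tai-chi truly does in these patients. It is not called a mediation or dose-response analysis.

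In Instruments, item 7 (socio-demographic and clinical information), the article says "The frequency and duration of exercise or relaxation practices will also be recorded". The item goes on to extrapyramidal symptoms, medication and adjunctive treatments, and ends: "These factors can represent important confounding variables when modeling outcomes". It does not say at which visits these are recorded.

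Item 6.3, on sleep, smoking, drinking and diet on the day of saliva collection, says: "All the above measures will affect the diurnal cortisol rhythm and hence must be taken into account during data interpretation".

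Under Participant recruitment, the sample size is also based on regression: "Experimental, clinical and demographic variables anticipated to affect the intervention outcome were included in the model".

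**The concern.** A confounder is a common cause of treatment and outcome. In a randomised comparison, a variable that the arm itself changes cannot play that role. Practice frequency is the amount of treatment taken up, so it lies on the path from allocation to outcome. Holding it fixed has two consequences.

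- It takes out whatever part of the benefit works through practising.
- It compares people who practised equally despite different allocations. These groups are no longer alike if, say, motivated or less ill participants practise more.

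The model is linked in the text to the true effect of Tai-chi. A reader could therefore take its arm coefficient as the better estimate, when it answers a different question and may be biased even for that one. Adjusting for uptake also sits badly with the intention-to-treat aim stated in the same section.

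**Working it through.** **1. Is practice a consequence of the arm?** Three places in the protocol article bear on this.

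- Participant recruitment: an inclusion criterion requires no formal training in, or regular practice of, Tai-chi. Tai-chi practice at baseline is therefore near zero by design.
- Intervention: the two active arms get a weekly 1-hour class for 12 weeks and are invited to 45-minute guided sessions twice a week. Waitlist is offered a class only after the 24-week assessment.
- Background: continued practice is encouraged once classes end.

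Variation in Tai-chi practice thus arises after allocation and because of it.

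**2. Formula.** Let T be the total effect of arm on outcome, Δ the difference in mean practice between arms, and k the within-arm slope of outcome on practice. In a linear model with arm and practice,

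adjusted arm coefficient = T − kΔ, with k = b + c,

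where b is the causal effect of a unit of practice and c is the extra slope from an unmeasured trait that drives both practice and outcome. The document gives none of these quantities; every value below is an assumption.

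**3. Mediation only (c = 0).** If a share p of T acts through practice, bΔ = pT and the coefficient is T(1 − p). With T = 0.50 SD:

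- p = 30%: 0.50 × 0.70 = 0.35
- p = 60%: 0.50 × 0.40 = 0.20
- p = 90%: 0.50 × 0.10 = 0.05

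**4. Precision against waitlist.** Assume practice has mean 1.5 and SD 0.6 in Tai-chi and is zero in waitlist. With equal arms, the variance inflation factor is 1 + (Δ²/4)/W, where W is the average within-arm variance of practice. Here Δ²/4 = 0.5625 and W = 0.36/2 = 0.18, so the factor is 1 + 0.5625/0.18 = 4.1 and the standard error is multiplied by √4.1 = 2.0. A simulation with 400,000 per arm and waitlist practice only close to zero gave 3.77, a multiplier of 1.94.

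**5. Mediation with a shared trait.** The simulation used 38 per arm (153/3 = 51, times 0.75), 3,000 runs, T = 0.50 on the simulated outcome scale, and practice with SD 1 and Δ = 2. A trait loading of 0.5 on both practice and outcome gives c = 0.5 × 0.5 = 0.25.

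| Scenario | T − (b + c)Δ | Simulated, unadjusted | Simulated, adjusted |
|---|---|---|---|
| Half through practice, no trait | 0.50 − 0.125 × 2 = 0.25 | 0.50 | 0.25 |
| All through practice, no trait | 0.50 − 0.25 × 2 = 0.00 | 0.50 | 0.00 |
| None through practice, trait | 0.50 − 0.25 × 2 = 0.00 | 0.50 | 0.00 |
| Half through practice, trait | 0.50 − 0.375 × 2 = −0.25 | 0.50 | −0.26 |
| All through practice, trait | 0.50 − 0.50 × 2 = −0.50 | 0.49 | −0.51 |
| Practice equal in both arms (Δ = 0), trait | 0.50 − 0 = 0.50 | 0.50 | 0.50 |

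Where the coefficient falls to zero, including a variant with waitlist practice set exactly to zero, the arm was significant in 63% to 74% of runs without adjustment and in about 5% with it.

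**6. No true effect (T = 0, b = 0).** Let the trait raise the outcome by 0.3 per SD and correlate ρ with practice, with practice SD s and Δ = 1.5. The adjusted coefficient is −1.5 × 0.3ρ/s.

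- ρ = 0.78, s = 0.64: −0.55
- ρ = 0.5, s = 0.64: −0.35
- ρ = 0.5, s = 1.0: −0.225

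A spurious effect as large as −0.55 needs a strong link between trait and practice.

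**7. Sample size.** The inputs are "using multiple regression modeling with a medium effect size (f^2^) of 0.15, at 0.8 power and a significance level of 0.05" and 25% attrition. The number of predictors is not stated. Nine predictors give 114 analysable participants; 114/0.75 = 152, or 153 in three equal arms. This is consistent with the stated 153 but cannot be confirmed, and the point above does not depend on it.

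**The case against.** The strongest reply is that the effectiveness test is the ANOVA, and the regression is a second analysis of how outcomes relate to covariates. It gives no equation or covariate list, and its wording could describe a dose-response model. Covariate timing is commonly left to a fuller document. Practice in Instruments item 7 sits beside age and marital status and may mean background exercise habits.

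Much of this stands, and it rules out three stronger readings that a reader might infer.

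- *That the main comparison is spoiled.* The ANOVA names no covariates and is run by intention-to-treat. Nothing in the text shows that it is affected.
- *That the effect will be removed or reversed.* That is one possible result. Attenuation alone, or no change, is also possible. Tai-chi against exercise, the contrast meant to isolate what is unique to Tai-chi, may be nearly unbiased, since both arms have the same class and session schedule. It stays unbiased only if actual practice is similar.
- *That medication, extrapyramidal symptoms and the daily cortisol items are also misused.* Item 7 gives no timing and says only that its factors can be confounders; baseline values would be proper covariates. Item 6.3 speaks of interpreting cortisol data, not of a covariate in a treatment-effect model.

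The practice point is not answered. The Data analysis sentence concerns the role of Tai-chi, names frequency of practice, and claims insight into true effects without labelling the model exploratory. The entry criteria leave little baseline Tai-chi practice for it to mean. This is a stated causal role, not a detail left for later.

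**Conclusion.** The point holds for the OLS model with frequency of practice. Its arm coefficient is not the randomised effect of Tai-chi and should not be read as one. Against waitlist, a true 0.50 SD effect would appear as 0.35 to 0.05 SD when 30% to 90% of it acts through practice, with a standard error nearly twice as large. A trait that raises both practice and outcome can turn the sign. These sizes rest on assumed practice distributions, mediated shares and trait loadings, and illustrate direction and possible scale rather than predict the trial's results. The intention-to-treat ANOVA is outside the finding. The other item 7 and item 6.3 variables come within it only if their 12- or 24-week values would be used as covariates, which the text does not state.

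**What to change.** Reword the regression paragraph in Data analysis, and the closing sentence of Instruments item 7, as follows.

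- In any model used to estimate the effect of Tai-chi, adjust only for values measured before randomisation, including the baseline value of the outcome.
- Report frequency of practice in a separate analysis labelled exploratory dose-response or mediation, with its assumption of no unmeasured common cause of practice and outcome stated. Do not present the arm coefficient from that analysis as the true effect of Tai-chi.
- State when the item 7 and item 6.3 variables are measured. If 12- or 24-week values of medication, extrapyramidal symptoms or the daily-condition items would enter a model, apply the same rule to them.

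The same data are used and the sample size is unchanged; the cost is wording only.
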